# Cross-sectoral follow-up after hospital discharge from a geriatric ward: a study protocol of a randomised controlled trial (G-UD)

**DOI:** 10.1186/s13063-025-08922-7

**Published:** 2025-07-01

**Keywords:** Geriatrics, Post-discharge follow-up, Readmission, Randomised controlled trial, Acute readmission, Older adults, Community-dwelling, Home care, Transitional care management, Discharge

## Abstract

**Background:**

Advancing age is associated with multimorbidity, polypharmacy and functional impairments and older adults with these characteristics are at increased risk of acute admission and readmission. Readmission rate of geriatric patients is high, especially within the first week after discharge. Previous studies on transitional care interventions have mainly showed positive effects, but no study has assessed the effect of a home visit done jointly by a geriatric nurse and a community nurse, with a systematic review of health functions, objective clinical assessment and bedside blood analyses.

**Methods:**

A single-centre two-arm parallel group randomised controlled trial using permuted block randomisation will be conducted. Randomisation occurs at discharge. The intervention consists of a follow-up visit within 2–5 days by a geriatric nurse and a community nurse. A systematic review of bodily functions is carried out, and solutions of identified problems are discussed taking into consideration the patient’s view. If the patient shows signs of worsened health since discharge vital status and bedside blood analyses using point-of-care-testing (POCT) can be carried out at the discretion of the geriatric nurse. As required the patients will be conferred with a senior geriatrician by video consultation. The patient’s primary care physician is invited to participate online. The control group will receive usual discharge. Endpoints are readmission, mortality rates and financial costs. User perspectives include focus group interviews with patients, geriatric nurses, community nurses, geriatricians and primary care physicians.

**Discussion:**

The intervention is multifactorial to match the needs of complex geriatric patients. We will thus not be able to discern, which part of the intervention has the greatest impact, but the intervention will encompass most of the clinical situation that may potentially lead to acute readmission. If a positive effect is found the intervention may be scaled up to include all departments discharging vulnerable geriatric patients, as well as implemented in guidelines for the discharge of older medical patients.

**Trial registration:**

ClinicalTrials.gov, Identifier: NCT05139823, Registered 1 December 2021.

**Supplementary Information:**

The online version contains supplementary material available at 10.1186/s13063-025-08922-7.

## Background

Geriatric patients are characterised by high age, multimorbidity and polypharmacy, frequently in combination with functional impairments [1, 2]. This makes them frail and particularly vulnerable to an increased risk of acute hospital admissions and readmissions [3, 4]. Despite the ongoing demographic change towards more old and oldest olds [5, 6], the number of hospital beds has been reduced markedly [7], mainly achieved by reducing in-hospital length of stay (LOS) [8]. At the Department of Geriatrics, Odense University Hospital (G-OUH) LOS declined from 11 days in 2006 to 6 days in 2023 (personal communication). Consequently, older patients are discharged in a more vulnerable state than previously, but with care support delivered by the municipal home care.

In Denmark, readmissions occur in about 10% of 65 + year old [9] but increases with higher age [10]. The risk of readmission increases with the number of comorbidities, medications and prior contacts to the primary health care providers [10], all being characteristics of the geriatric patient.

For geriatric patients admitted to G-OUH, readmission occurs in 19% of discharged patients according to hospital administrative data, and the median number of days until readmission is nine [11]. Most patients are readmitted with a diagnosis unrelated to their index admission, with pneumonia and dehydration being the most common causes—even when these were not the primary diagnoses at the time of the index admission.[11].

Several intervention studies aiming at reducing acute readmission by post-discharge follow-up exist [12]. A recent systematic review of transitional care interventions consisting of both pre- and post-discharge components found that transitional care interventions reduce readmissions among older medical patients [13]. However, the review includes several older studies as well as studies from countries not comparable to Denmark due to differences in the health care systems, and the overall conclusion is that high-quality studies are lacking [13]. In Denmark, two randomised controlled studies examining acute 30-day readmission among geriatric patients, i.e., non-disease-specific multimorbid older adults with functional loss have emerged within the last 3 years [14, 15], which both showed significant reductions in acute readmissions after post-discharge follow-up. However, one of the studies was quasi-randomised and included geriatric patients discharged from the emergency department [14]. The other study included patients discharged from a geriatric department, but the ward staff was non-blinded to intervention allocation [15]. Furthermore, in this study the intervention was carried out by hospital staff, i.e., a geriatrician and a nurse or physiotherapist, while the home care was invited to join, but not as a necessity.

A recent before-and-after study in geriatric patients discharged to a municipal intermediate care facility has shown that post-discharge follow-up visits by a team consisting of a specialist physician in geriatric medicine and a geriatric nurse reduce acute 30-day re-admission by 28% [16]. Qualitative data from interviews of staff from the same study indicates that the geriatric team visit gives the municipal nurses at the intermediate care facility a feeling of self-confidence and feeling of increased competencies when working interdependently [17]. This supports the concept of a face-to-face cross-sectoral exchange of information on health and care in the presence of the newly discharged patient is important to cover all aspects of health recovery.

The number of health professionals dedicated to older patients does not balance the growing number of diseased older people [18]. Digital technology offers a possibility for alleviating the challenges of scarce personnel resources. Geriatricians may function as virtual consultants by video [19], thereby supporting experienced geriatric nurses with competences in doing objective clinical assessment as well as collecting and analysing biological samples on-site. The increased digitisation in health care together with the development of various bed-side point-of-care testing (POCT) technologies, e.g., biochemical analyses, ultrasound, has increased the possibilities for more efficient and high-quality health services without jeopardising the safety of older vulnerable patients. There is an urgent need to examine the effect, as well as the challenges, in using digital health services for clinical decision-making on discharged geriatric patients during the first vulnerable days at home after discharge. We hypothesise that the in-person meeting between a geriatric hospital nurse and a community nurse, who works closely with the municipal home carers can reduce acute readmission and other challenges related to the transition by early identification of health-related problems arising immediately post-discharge.

In this article, we present the protocol for a planned RCT, which will be conducted to examine an intervention that helps alleviating the challenges related to transition from a specialised acute hospital ward to the geriatric patient’s home and personal care provided by the municipal home care. We present our study, with a thorough description of our methods.

## Methods

This paper follows the SPIRIT 2013 statement [20]. No large language models or other AI has been used in the creation of this manuscript.

### Aim

The aim of this study is to investigate the effects of a coordinated and simultaneous home visit 2–5 days after discharge, by a community nurse and a geriatric nurse equipped with POCT equipment on 30-day readmissions.

### Study design

The study is a single-centre two-arm parallel group randomised controlled trial with an aim to show superiority. It will utilise permuted block randomisation without stratification. Distribution will be equivalent between the two groups. The study will be conducted over approximately 24 months.

### Setting and study population

The study will take place at the Department of Geriatrics Odense University Hospital Region of Southern Denmark (G-OUH) and in the Odense Municipality, Denmark.

Odense Municipality is by population the largest municipality in the Region of Southern Denmark and the 4th largest municipality in Denmark [21]. The population (2022) is approximately 206,000 [21], of which approximately 36,000 are 65 + years of age [21]. Odense Municipality has 14,000 employees [22], including 3500 employees caring for frail older adults and disabled persons [23]. This includes both care at home and public care homes. The mean life expectancy in Odense Municipality is 81.2 years (2018–2022) [24]. In 2021, 5500 citizens received home care [25]. The municipal home care is extensive and covers housing for older citizens, cleaning, personal care, help taking medication, physical training, provision of aids and appliances and help carrying out activities of daily living. The municipal home care works 24/7 and delivers care at home based on a needs assessment. The municipality also provides 1123 care home dwellings (i.e. “1123 dwellings” in care homes), not including dwellings in private care homes (*n* = 449). Furthermore, home care service is allocated to the individual citizen based on a needs assessment, and irrespective of the presence of a cohabitating partner. If a family member provides care for a relative, they can apply for respite or relief [26].

The municipality employs social and health care workers as well as nurses (community nurses; home-based-care nurses) to provide care and nursing care. All citizens are allocated a primary care physician, who serves as the gatekeeper to the hospital. The Danish health care system offers a universal health care coverage financed through taxes [27].

Odense University Hospital is a medium-sized university hospital situated in Odense municipality. It has 965 beds, 95,000 annual discharges and approximately 315,000 patient-days of admissions per annum. The hospital provides 412 of 652 highly specialised functions and approximately 10,000 employees [28]. Odense University Hospital primarily covers the island of Funen, Denmark, but has also many highly specialised functions offered both as regional functions and at a national level. It is the largest hospital in the Region of Southern Denmark and the second largest hospital in Denmark by number of beds.

The Department of Geriatric Medicine at Odense University Hospital is a specialised medical department with geriatric specialist consultants caring for up to 32 in-hospital beds and a large outpatient clinic. In 2018, there were 2232 unique patients discharged from the ward. The mean age was 82.4 years, and the mean LOS was 6.1 days. The Department of Geriatric Medicine at Odense University Hospital receives acutely admitted geriatric patients, which are characterised by medical complexity, high age, multimorbidity, polypharmacy and functional loss. Medically non-complex patient with a simple single disorder (e.g. otherwise healthy adult with pneumonia) are allocated to any specialised internal medicine ward but may also be allocated to G-OUH according to availability of beds. However, due to the vast number of older medically complex patients, simple single disorder patients are few at G-OUH. The most common primary discharge diagnoses of patients discharged from G-OUH are acute infections and dehydration, but with considerable overlap with a variety of other common diagnoses, e.g. falls, rhabdomyolysis, heart failure, chronic obstructive pulmonary disease (COPD) and delirium.

All G-OUH patients are initially assessed in the acute medical unit (AMU). Patients are either referred to the AMU by their primary care physician or a doctor on call or may have called the emergency services. Upon arrival in the AMU, they are seen by AMU physicians. The acute medical unit physicians making the initial assessment are specialists of acute medicine or specialists of any internal medicine speciality (gastroenterology, rheumatology, pulmonology, endocrinology, infectious diseases or geriatric medicine). Patients admitted with cardiac symptoms are initially assessed by a physician from cardiology before going to either the AMU or the cardiology ward. Patients allocated to G-OUH are transferred to the geriatric ward if total LOS is expected to be greater than 48 h. This is determined in the AMU by either a geriatric team (physician, physiotherapist, occupational therapist and nurse) during daytime or by the AMU physician on duty during evening or night. If the LOS is expected to be less than 48 h for a patient allocated to G-OUH, the patient will be treated in the AMU by the geriatric team, but not physically moved to the ward. If continued intravenous treatment is necessary, the geriatric team can discharge the patient to their home, where the treatment can be continued and monitored by a municipal acute home care team equipped with point of care blood sampling. Occasionally, patients expected with a shorter stay are transferred to G-OUH, due to crowding in the AMU.

### Eligibility

A project coordinator identifies eligible patients among all patients admitted to G-OUH.

Only patients transferred to G-OUH ward are screened for eligibility, and thus patients discharged directly from the AMU are not included.

Criteria for eligibility are patients admitted to G-OUH and discharged to their own home and in need of personal care provided by the municipal home care organisation in Odense Municipality. Patients discharged to care home are also included. Exclusion criteria are patients discharged to other skilled nursing facilities or discharged with no need for personal care. Also, terminally ill patients and incapacitated patients, e.g., patients with moderate or severe dementia are not eligible. Patients with dementia are excluded if they are unable to live independently (i.e., if they require a care home or are completely dependent on their spouses to remain at home). In cases of uncertainty, a senior geriatric consultant will assess the cognitive function and determine severity. Patients that are delirious throughout the entire hospital stay will also be excluded, as they cannot give informed consent. Patients with active delirium are reassessed by a project manager based on indications such as confusion to orientation (to personal data, treatment, location, time and recent events), ability to concentrate and follow a conversation, organisation and coherence of thought, and overall mental status, as assessed by the CAM score. In cases of uncertainty, patients are not included. Finally, while initially excluding readmitted patients who had already been enrolled as study participants, it was decided after 4.5 months from the start of the study to allow the inclusion of readmitted study participants. The change was made due to an insufficient entry of eligible participants following a shortage of staff and a cut in the number of hospital beds at G-OUH. The original eligibility criteria were thus slightly changed to allow readmitted patients to participate. We decided to include these patients due to the uncertainty of future patient flow, knowing that we can adjust for this factor in the analyses after the trial.

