**Fig. 1 Fig1:**
[figure not shown]
Study design

Eligible patients are informed about the project (orally and in writing) and invited to join. If they accept, they sign an informed consent. They are randomised on the day of discharge to either the intervention or control group. In the case of a planned discharge during the weekend, the participants are randomised on Friday. Participants randomised to the control group receive a usual discharge, while participants in the intervention group receive a usual discharge as well as a coordinated follow-up visit, which is planned to take place 2–5 working days after the day of discharge.

For all participants (control and intervention), administrative and clinical data will be collected from hospital records and the hospital administrative system, e.g. hospital discharge diagnoses, LOS, medication, medical history, Charlson Comorbidity Index [29] and Barthel Activities of Daily Living (ADL) score.

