### Blinding

The participant, hospital staff and project coordinator are blinded to the allocation until the participant is discharged upon which the randomisation occurs. Thus, the hospital treatment and discharge should not be affected by the enrolment of the participant. After discharge, when the patient is randomised, the participant, the project coordinator, the geriatric nurse, the community nurse, and the primary care physician will no longer be blinded. The project coordinator is not involved with the patients after the patient has been discharged, except if the patient is readmitted and invited to participate in the project again.

Prior to data analysis, all IDs will be linked to a new scrambled ID, and the old ID is hidden as will all identifying data (social security number, address). This will be done by a third party to ensure that the data analyst will not know which group is the intervention and which is the control group. All data analysis will thus be done blinded.

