***Secondary outcomes***		
Outcome 3	Mortality (1 year)	Proportion of participants deceased within one year
Outcome 4 Outcome 5	Time to Readmission Days alive out of hospital	Proportional hazard model of readmission with a total duration of 1 year and median time to readmission estimated by Kaplan–Meier method Days spent alive out of the hospital within 30 and 90 days from discharge
Outcome 6	Clinical assessments/POCT measurements and their association to decision making	Regression analysis of the association between conducting a clinical measurement (e.g. Saturation, temperature, Sodium, CRP) or POCT analysis and the risk of readmission
Outcome 7	Costs associated with the intervention	Analysis of the costs associated with the intervention and potential savings from the result of the intervention
Outcome 8	User perspectives among involved participants and professionals	Analysis of questionnaires and focus group interviews with involved groups, including participants, community nurses, geriatric nurses, geriatric physician, and primary care physician

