### Analyses of primary and secondary outcomes

The primary outcome is 30-day acute readmission. We will use relative risks to compare the readmission rates in the two groups. Relative risk for other readmission time frames will also be calculated to improve comparisons with other studies.

Competing risk of death will be considered in our analyses, as it can skew the results. Partially due to this, days out of hospital will also be calculated as it is less affected by the competing risk of death than a binary readmission outcome.

We will also calculate the relative risks for 30-day mortality.

A proportional hazard model will be used to explain the time to readmission. This will be done using the Cox regression model. Moreover, median time to readmission will be estimated by the Kaplan–Meier method.

We will include relevant patient characteristics that are known risk factors in our statistical analyses, e.g. multimorbidity, polypharmacy and length of stay.

Throughout the analyses, we will adjust for participants that were already readmitted at the time of recruitment. Separate analyses will be done for patients that already received the intervention, as there may be a residual effect of the intervention.

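### Re-enrolled participants can hold several records with overlapping follow-up, and the stated adjustment does not remove deaths or hospital days shared between those records

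*Protocol article*

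**What the plan says.** The Eligibility section reports that "it was decided after 4.5 months from the start of the study to allow the inclusion of readmitted study participants". It gives slow entry of eligible patients as the reason and justifies the change by "knowing that we can adjust for this factor in the analyses after the trial". The Blinding section confirms repeat entry: the coordinator has no contact with patients after discharge "except if the patient is readmitted and invited to participate in the project again". Trial status repeats that this can be dealt with in the analysis.

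On allocation, Recruitment and enrolment says of consenting patients: "They are randomised on the day of discharge to either the intervention or control group". Study design adds "Distribution will be equivalent between the two groups", with no stratification. No separate rule is given for a person who enters a second time.

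On outcomes, Table 2 lists "Proportion of participants deceased within one year" and "Days spent alive out of the hospital within 30 and 90 days from discharge". Analyses of primary and secondary outcomes adds 30-day mortality, which is also examined at the interim. Under Data collection, death and readmission are followed for one year from each participant's allocation date.

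The remedy is in Analyses of primary and secondary outcomes: "Throughout the analyses, we will adjust for participants that were already readmitted at the time of recruitment". Separate analyses are also planned for patients who already had the intervention, because its effect may persist. The sample size section counts patients: 763 per group, 1526 in total, 1832 with a dropout allowance.

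**The concern.** A person who enters twice has two allocation dates and two follow-up clocks, and the first clock is still running when the second starts. Three things follow.

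- **Shared events.** One death can be a 30-day or 1-year death in both records. Days at home or in hospital after the second discharge belong to both 30/90-day windows.
- **Crossover inside the first window.** A first-time control who is later allocated to the intervention is visited while the control record is still being followed.
- **Unit of analysis.** The sample size rests on independent patients, but repeat entry was introduced because too few patients were available. The target could therefore be met in enrolments.

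A term for already-readmitted status shifts the expected outcome of a record. It does not delete the second copy of a death or a day, undo crossover or model correlation within a person. As worded, it also does not separate former controls from former intervention patients. At stake are mortality, including the 30-day mortality examined at the interim, days alive out of hospital, and the meaning of the sample size.

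**Working it through.** **1. Do the windows overlap?** Median time to readmission is 9 days (Background) and mean stay is 6.1 days (Setting and study population, 2018). A rough second discharge day is 9 + 6.1 = 15.1. Overlap with the first record is then:

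- 30-day window: 30 − 15.1 = 14.9 days, about half
- 90-day window: 90 − 15.1 = 74.9 days, about five-sixths
- 1-year window: 365 − 15.1 ≈ 350 days

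Example: discharged day 0, readmitted day 9, discharged again day 15, died day 25. The death is on day 25 of the first record and day 10 of the second, so it lies in both 30-day windows. A visit 2–5 working days after the second discharge also falls inside the first 30 days.

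**2. Is the binary readmission outcome counted twice?** No. Either the acute readmission that brings the person back has already made the first record positive, or the first window has closed. A further readmission counts only for the second record. The same holds at 90 days and for time to first readmission.

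**3. The plan's sample size.** Inputs: p1 = 0.19, p2 = 0.19 × 0.72 = 0.1368, difference d = 0.0532, mean p = 0.1634, two-sided alpha 0.05, power 0.80.

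n = [1.960·√(2 × 0.1634 × 0.8366) + 0.8416·√(0.1539 + 0.1181)]² / 0.0532² = (1.0248 + 0.4389)² / 0.002830 ≈ 757, or 758 with unrounded values taken up to the next integer.

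The stated 763 is close, and power at 763 per group is 0.803.

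**4. Repeat records if 1526 counts enrolments.** Let q be the assumed share of 30-day readmissions that re-enrol, and a = 0.1634q. Then:

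- unique persons = 1526(1 − a)
- repeat records = 1526a
- persons with two or more records = unique × a
- share of these in both arms, with independent 1:1 re-randomisation = 1/(2 − a)
- first-enrolment power = Φ[(0.0532·√(unique/2) − 1.0248)/0.5215]

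| q | Unique persons | Repeat records | Two or more records | In both arms | Power |
|---|---|---|---|---|---|
| 25% | 1464 | 62 | 60 | 31 (51%) | 0.79 |
| 50% | 1401 | 125 | 114 | 60 (52%) | 0.77 |
| 75% | 1339 | 187 | 164 | 87 (53%) | 0.75 |
| 100% | 1277 | 249 | 209 | 114 (54%) | 0.73 |

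As a share of all persons, those in both arms run from 31/1464 = 2% to 114/1277 = 9%. Re-enrolment after day 30 would add to these counts.

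**5. Error rate and bias.** A simulation used 3000 runs per scenario, 1350 unique persons, independent 1:1 allocation at each entry, assumed 1-year mortality of 30%, and q of 50% or 100%.

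- With no effect, analysing all records as independent rejected in 4.6–5.7% of runs for readmission and 5.1–5.5% for mortality. Simulation error is √(0.05 × 0.95/3000) ≈ 0.4 percentage points.
- With an assumed mortality RR of 0.80 for anyone ever visited, the all-records RR was 0.82 (q = 50%) and 0.85 (q = 100%). The first-enrolment RR was 0.81 and 0.83.
- With a true readmission RR of 0.72 and an assumed carry-over factor of 0.8 on later readmission risk, the all-records readmission RR was 0.72 at both values of q. Carry-over of that proportional form hardly moves the ratio. Other forms were not simulated.

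**The case against.** The strongest reply has four parts.

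**Adjustment is a broad word.** The article does not say covariate, and person-clustered errors with a prior-allocation term are themselves an adjustment. Model detail may sit in an analysis plan that is not shown. This stands in part: missing detail is no fault, and a reader should not infer that no analysis could cope. But the article names the factor to be adjusted for, already-readmitted status, and uses that remedy to justify the eligibility change. For shared deaths and days that remedy is inadequate.

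**The outcomes are worded per participant.** Record-level counting of deaths is an inference, and so is re-randomisation. Both are fair cautions. The wording still gives no answer for a person with two allocation dates. If the old allocation were kept instead, nobody would be in both arms, but a duplicated death would count twice in the same arm.

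**Carry-over is acknowledged.** It is, and the planned separate analyses single out prior intervention patients. The text does not say whether those records stay in the main comparison. If they stay, that comparison is unchanged. If they are removed, former controls still appear twice.

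**The effect is small.** A reader might infer that the primary result is double-counted, that false positives rise, or that much of the sample sits in both arms. Steps 2, 4 and 5 of the working support none of these. Most of the dilution in mortality comes from later crossover, which first-allocation analysis also leaves in place.

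**Conclusion.** The point holds for mortality (30-day and 1-year, including the interim check) and for days alive out of hospital. Repeat entry lets one death or one stretch of days sit in two records, and the stated remedy does not remove it. In the simulation, duplication moved the mortality RR by only 0.01–0.02 beyond what crossover does anyway, so this is a modest distortion and not a threat to the trial's validity.

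For readmission, the concern is limited to carry-over, the unit of analysis and the patient count. If the 1526 were filled with enrolments, a first-enrolment analysis would have power of about 0.79–0.73. Whether all records or first records should be primary for readmission is a genuine trade-off that the documents do not settle.

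The size rests on assumptions: the re-enrolment share (not given), independent 1:1 re-randomisation (implied), 30% 1-year mortality, and the rough day-15 figure, which adds a median to a mean. Severity: should-fix.

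**What to change.** Amend the analysis wording before the data are unmasked:

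1. **Mortality and days alive out of hospital.** Count each person once, from the first randomisation and under that allocation. State that later crossover remains and dilutes the effect.
2. **30-day readmission.** If all randomised discharges are kept, estimate the RR with person-clustered standard errors (for example modified Poisson or GEE) and a term for prior allocation. Report a first-randomisation-only analysis alongside.
3. **Allocation of re-entrants.** State outright whether they are randomised afresh, and whether records with a prior intervention stay in the main comparison.
4. **Counts.** Report unique persons as well as records against 1526 and 1832, and restate power if the target is met only in records.
5. **Interim.** It was scheduled for January 2024, so confirm how repeat records entered the 30-day mortality and readmission comparisons.

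The cost is wording and analysis time, with no new data collection. The downside is fewer records for the secondary outcomes; the readmission analysis can keep all of its records.
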